## Abstract

**Introduction:**

Functional gastrointestinal disorders (FGIDs) affect over 40% of individuals globally, and impact the quality of life. A significant portion of FGIDs patients comorbids with anxiety and depression. Traditional screening tools for psychological disorders may lack comprehensiveness. Vibraimage technology currently enables non-contact, objective analysis of psychological indicators through high-frame-rate cameras and computer analysis of micro-movements. Therefore, this study aims to (1) explore the use of vibraimage technology as a non-contact objective method to assess the psychological status of FGIDs patients, comparing this technology with the Hospital Anxiety and Depression Scale (HADS) to evaluate its screening efficacy, and (2) observe the therapeutic outcomes of FGIDs patients with or without comorbid psychological disorders after the same conventional treatment.

**Methods:**

This is a prospective, single-center observational trial. 276 FGIDs outpatients who visit Peking Union Medical College Hospital will be evaluated simultaneously by HADS and vibraimage technology, then to evaluate the screen efficacy of this technology. The patients will be allocated into two groups (those with or without psychological disorders). The primary endpoint is the overall rate of improvement, specifically referring to the proportion of patients who achieved Likert scores greater than or equal to 4. The secondary endpoints encompass evaluating whether there is a reduction of more than 50% in symptom evaluation scores such as IBS-SSS. Additionally, the study will assess changes in health status and quality of life using SF-36 questionnaires and the patients’ satisfaction with treatment. Furthermore, psychological status will be reassessed by vibraimage technology and HADS after treatment to evaluate the effect of combined psychological factors on FGIDs treatment.

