### Baseline data collection

2.3

Vibraimage data specialist is responsible for collecting and analyzing the patient’s vibraimage technology data, while the HADS assessment specialist will handle the general information collection and analysis of the patient’s HADS self-rating data. Both specialists are unaware of each other’s datasets. The physicians will solely administer conventional treatments based on FGIDs diagnostic criteria, without any knowledge of the results obtained from vibraimage technology or HADS questionnaires.

The following information will be collected: demographic data (age, gender, height, weight), marital and childbearing status, occupation and education level; disease-related details including course of illness, diagnosis and classification of FGIDs, treatment process, and dietary habits. The FGIDs symptoms will be generally assessed by5-point Likert score. Patients diagnosed with irritable bowel syndrome will be evaluated based on their IBS Severity Score (IBS-SSS) (19); patients with functional dyspepsia, as well as those with constipation, will be assessed using the relevant symptom scores (20, 21); while patients with other functional disorders will be evaluated through the Gastrointestinal Symptom Severity Index (GISSI) (22). Baseline questionnaires will be administered to assess anxiety and depression levels using the Hospital Anxiety and Depression Scale (HADS), and general health-related quality of life using the Health Status Questionnaire (SF-36) (23).

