#### The assessment of patient prognosis and satisfaction

2.6.2

The patients will be divided into two groups according to HADS, that is with or without psychological disorder group. The patients in both groups will receive the conventional treatment, without any additional interventions beyond the standard care for FGIDs. The treatment effect questionnaire will be administered after 4 weeks. Overall improvement will be evaluated using a 5-point Likert scale (36), where patients will be prompted to complete the following statement: “How does my gastrointestinal condition compare to before I commenced treatment at the clinic?” The response options include: deteriorated, slightly deteriorated, unchanged, slightly improved, and significantly improved. The HADS and vibraimage technology will also be systematically evaluated.

Primary endpoint: the overall rate of improvement, specifically referring to the proportion of patients who achieved Likert scores greater than or equal to 4.

Secondary endpoint: HADS and vibraimage technology outcomes, along with the improvement degree of FGIDs symptom scores such as IBS-SSS, quality of life by SF-36 questionnaires, and the patients’ satisfaction with treatment.

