### Descriptive statistics

2.9

The consistency analysis is conducted based on Gwet’s Agreement Coefficient 1 (AC1, 38) to assess the concordance between vibraimage technology and HADS detection results, as well as to determine the optimal threshold for vibraimage technology. Specifically, a HADS-A score of 8 or higher indicates anxiety, while a HADS-D score of 8 or higher suggests depression (10).

The measurement data that conform to a normal distribution are represented by *x̄* ± *s*, while the ones that do not conform are represented by the median (interquartile range). The difference between the two groups of measurement data following a normal distribution is assessed using a student *t*-test, whereas the difference between the two groups of measurement data not following a normal distribution is assessed using Mann–Whitney U test. The difference between the two groups is evaluated using *χ*^2^ test. Oneway-ANOVA analysis is employed for group comparisons. Pearson correlation analysis is used for measurement data with a normal distribution, and Spearman correlation analysis is used for measurement data without a normal distribution.

In the process of conducting binary logistic regression analysis to determine whether patients with FGIDs are also affected by psychological disorders, we will continuously enhance the model’s goodness of fit by eliminating irrelevant independent variables. Subsequently, a diagnostic model with high diagnostic efficiency will be derived. Finally, a Receiver Operating Characteristic (ROC) curve will be constructed based on the performance of sensitivity and specificity at various thresholds. This analysis will aid in identifying the optimal diagnostic test threshold and in evaluating the accuracy, sensitivity, and specificity of the test.

Variables with a *p* value <0.05 are considered statistically significant. The statistical analysis will be conducted by a medically trained personnel who will remain blinded to the assignment of study groups. The data statistics in our study will be conducted using paper questionnaires. In the event of missing items, we will either discard the questionnaire or, if necessary, employ imputation techniques to fill in the missing values.

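### The abstract defines the secondary symptom endpoint as a fall of more than 50%, section 2.6.2 only as an undefined degree of improvement, and the two can disagree if the HADS groups differ at baseline

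*Protocol article*

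**What the plan says.** The abstract (Methods) says that the secondary endpoints encompass "evaluating whether there is a reduction of more than 50% in symptom evaluation scores such as IBS-SSS". That is a binary outcome for each patient.

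Section 2.6.2, under the secondary endpoint, lists "the improvement degree of FGIDs symptom scores such as IBS-SSS". It does not say whether this means change in points, percentage change or a responder status, and it gives no threshold. Nor does any other section of the body.

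The groups compared on this endpoint are defined by the baseline questionnaire: "The patients will be divided into two groups according to HADS, that is with or without psychological disorder group".

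Section 2.3 assigns the score by diagnosis. "Patients diagnosed with irritable bowel syndrome will be evaluated based on their IBS Severity Score (IBS-SSS"), dyspepsia and constipation have their own symptom scores, and "patients with other functional disorders will be evaluated through the Gastrointestinal Symptom Severity Index (GISSI"). These scores are collected at baseline.

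For two-group comparisons, section 2.9 offers a t-test ("The difference between the two groups of measurement data following a normal distribution is assessed using a student" t-test), Mann–Whitney for non-normal data, and a chi-square test. It states no baseline adjustment for this endpoint. The logistic regression described there models the presence of psychological disorder, not response to treatment.

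**The concern.** The two descriptions lead to different analyses. A fall of more than 50% is a proportion, compared by chi-square. A degree of improvement reads most naturally as a quantity, compared by t-test or Mann–Whitney. A reader of the article cannot tell which one is the endpoint.

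In a randomised comparison this would matter less, because baseline scores would be balanced in expectation. Here the groups are formed by HADS status, and entry requires no minimum symptom score, so nothing in the design makes their baseline symptom severity alike. A percentage threshold scales the required fall with the starting score: more than 150 points from 300, more than 75 points from 150. A change in points does not scale in this way. With unequal baselines, one definition can show a group difference where the other shows none.

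At stake is the study's second aim, which is to see whether patients with and without psychological comorbidity respond differently to the same conventional treatment. This endpoint is one of several secondary measures that inform it.

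**Working it through.** **1. The plan's own figures.** The document gives no figure for the symptom-score endpoint. Its two sample sizes were reproduced to see whether either depends on it.

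- Follow-up (section 2.7): P1 = 0.57, P2 = 0.57/2 = 0.285, two-sided α = 0.05, power 0.80, 1:1, unpooled variance. n = (1.96 + 0.8416)² × (0.57×0.43 + 0.285×0.715)/0.285² = 43.4, so 44 per group. 44/0.90 = 48.9, so 49 per group and 98 in total, as stated.
- Diagnostic part (section 2.7): 1.96² × 0.8 × 0.2/0.07² = 125.4. Divided by the 50% prevalence this is 250.9, so 251. 251 × 1.1 = 276.1, stated as 276.

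The first rests on the overall improvement rate, the second on sensitivity. Neither uses the symptom scores.

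**2. Inputs for the comparison of the two readings.** All are assumptions, because the document gives no baseline scores and no model of improvement: an IBS-SSS-like score with baseline SD 70, mean 230 in group A, and mean 230, 280 or 320 in group B. The simulation kept baselines between 75 and 500 and follow-up scores between 0 and 500. The formulas below ignore these limits and agree closely with it.

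**3. Equal absolute improvement.** Change has mean 100 and SD 70 in both groups, independent of baseline.

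P(fall > 50%) = Φ[(100 − 0.5 × mean) / √(70² + 0.25 × 70²)], with denominator 78.3.

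| Baseline mean | Formula | Simulated >50% rate | Simulated mean fall (points) |
|---|---|---|---|
| 230 | Φ(−15/78.3) = 0.424 | 42% | 96 |
| 280 | Φ(−40/78.3) = 0.305 | 31% | 99 |
| 320 | Φ(−60/78.3) = 0.222 | 22% | 100 |

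The responder rates differ by about 11 or 20 percentage points, while the mean falls in points are nearly equal.

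**4. Equal proportional improvement.** The fall is 45% of baseline on average, SD 25 percentage points, in both groups.

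P(fall > 50%) = Φ[(0.45 − 0.50)/0.25] = Φ(−0.2) = 0.42 at every baseline. Mean fall in points = 0.45 × baseline mean.

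| Baseline mean | >50% rate | Formula, mean fall | Simulated mean fall |
|---|---|---|---|
| 230 | 42% | 103.5 | 104 |
| 280 | 42% | 126 | 126 |
| 320 | 42% | 144 | 144 |

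The responder rates now match, and the mean falls differ by about 22 or 40 points.

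**5. Equal baselines (230 and 230).** Both measures show no difference in either scenario. The disagreement comes from the baseline gap.

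**6. Adjusting for baseline.** In step 3 the expected follow-up score at a given baseline is baseline − 100; in step 4 it is 0.55 × baseline. Each is a straight line in the baseline score and the same line in both groups. A comparison of follow-up scores adjusted linearly for baseline therefore gives a group difference of zero in both scenarios, apart from a small distortion where scores are cut off at zero.

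**The case against.** The strongest reply is that section 2.6.2 does not contradict the abstract. It is only vaguer: the degree of improvement can be a general label that the abstract makes specific, and a journal article may leave detail to a fuller protocol or analysis plan. This stands in part. The wording in 2.6.2 is undefined, not a rival definition, and if it meant percentage change it would lean the same way as the 50% rule (simulated means of 45% against 37% or 33% in step 3 of the working). But the point concerns two statements that are both in the article. The threshold is in the summary and absent from the section that sets the endpoints, whereas the primary endpoint is worded the same way in both.

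A reader might infer more than this, in three ways that the document does not support.

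- That the 50% rule penalises patients with psychological disorder. This needs a higher baseline in that group and an improvement that is fixed in points. The document states neither; the introduction says only that comorbidity goes with poor response to conventional treatment. Under proportional improvement the rule is neutral.
- That the sponsor is free to choose the more favourable definition after seeing the data. The full protocol and analysis plan are not shown and may settle the matter.
- That responders are to be pooled across instruments. Section 2.3 assigns an instrument to each diagnosis, and no section says how, or whether, they are combined.

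Also correct is that replacing the 50% criterion with a change standardised by each instrument's SD would be a preference. One SD need not mean the same benefit on each scale any more than a halving does.

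**Conclusion.** The point holds as an inconsistency of definition with a possible effect on the conclusion. The article gives a threshold of more than 50% in one place and an unspecified degree of improvement in the other. These call for different tests and can disagree when baselines differ.

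The size is conditional. With an assumed baseline gap of 50 to 90 points, the disagreement is about 11 to 20 percentage points in responder rate (equal absolute improvement) or about 22 to 40 points in mean fall (equal proportional improvement). With no gap it vanishes. Neither definition is shown to be biased against either group. The endpoint is secondary; the Likert primary endpoint and the targets of 276 and 98 do not change.

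**What to change.** State one definition of the symptom-score endpoint, in the same terms, in the abstract and in section 2.6.2.

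For the analysis, compare the HADS groups on the diagnosis-specific score at 4 weeks, adjusted for its baseline value, instead of relying only on the unadjusted two-group tests in section 2.9. Show the result per instrument and do not pool raw points across scales. Report the rate of patients with a fall of more than 50% alongside it.

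The cost is a change of wording in two places and slightly more analysis. Baseline scores are already collected, so no new data are needed. There are two limits. Each instrument's comparison uses only the patients with that diagnosis and so is less precise than one on the whole sample. And the adjusted difference describes an association at equal measured baseline severity; between groups that were not randomised it is not a causal effect of psychological comorbidity.

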## Introduction

1

Functional gastrointestinal disorders (FGIDs), also known as disorders of gut–brain interaction (DGBI), manifest as a variety of gastrointestinal symptoms such as nausea, vomiting, abdominal pain, bloating, diarrhea, and constipation, which have been excluded organic lesions through objective examinations. Functional dyspepsia, irritable bowel syndrome and functional constipation are the most common FGIDs in clinical practice (1). The pathophysiological mechanisms of FGIDs are complex, involving abnormalities in gut–brain interaction, dysbiosis of intestinal flora, alterations in mucosal immune function, visceral hypersensitivity and gastrointestinal dysmotility (2). A large-scale epidemiological study showed over 40% of individuals worldwide suffered from FGIDs, which significantly impacting the quality of life (3). Recent studies have indicated that approximately 50% of FGIDs patients also experience comorbid anxiety and depression (4–6), which leads to a poor response to conventional treatments. As a result, these patients often require the use of neuromodulators in conjunction with cognitive-behavioral therapy to achieve clinical relief. In accordance with the Rome Foundation’s definitional guidelines, neuromodulators are divided into central and peripheral types, with central agents such as antidepressants, antipsychotics, and buspirone, and peripheral agents including serotonergic drugs, chloride channel modulators, and α2δ (delta) ligands (7). Most gastrointestinal specialists may lack a background in psychology. And up to now, there are no rapid and effective screening tools for identifying FGIDs patients comorbid with psychological disorders, resulting to recurrent visits, cost issues and substantial healthcare resource utilization (3, 8, 9).

Various scales based on psychological questionnaires may assess and screen mental health disorders, such as the Hospital Anxiety and Depression Scale (HADS), Patient Health Questionnaire-9 (PHQ-9), and Generalized Anxiety Disorder-7 (GAD-7). Among these, as for the simplicity, short time to assess, good reliability and validity, HADS has become a widely used self-assessment questionnaire to evaluate anxiety and depression (10). However, questionnaire-based screening entails some subjectivity and may not encompass other psychological status like anger and fear (11). Structured psychological interviews based on the diagnostic and statistical manual of mental disorders (DSM) offer a comprehensive evaluation of the patient’s psychological states but are relatively time-consuming and unsuitable as an initial screening tool (12).

The fact that physiological reflex movements reflect emotional and psychophysiological states has long been recognized (13). Greater uniformity, symmetry, and fluidity in movement are indicative of a normal and positive psychophysiological state, while irregularities, asymmetries, and lack of fluidity in movement suggest the presence of some pathological condition. Based on this, vibraimage technology studies the physiological features of reflex movements of the head at a micro-vibration level, beyond what is visible to the naked eye (14). This advanced, non-contact, non-interactive assessment method overcomes the subjectivity of traditional questionnaires. Utilizing high-frame-rate cameras, it captures micro-vibration movements of the head, neck, and facial muscles, which are then converted into pixel motion through computer analysis. This process captures three-dimensional trajectories and calculates the amplitude and frequency of vibrations for each pixel. Video motion magnification algorithms and comparisons with a basic feature model library enable the analysis of potential micro-expressions and various psychological indicators. This innovative technology is particularly useful in clinical settings, where it can monitor patient responses and detect subtle signs of distress or discomfort that might not be evident through standard observational methods (15–17).

This study aims to evaluate the psychological status of FGIDs patients using vibraimage technology and compare it with HADS to assess the clinical screening efficacy of this technology. By doing so, the study seeks to provide a theoretical basis for the significance of comorbid psychological disorders in FGIDs patients and the necessary of early multidisciplinary collaborative treatment for this patient population, ultimately improving their overall health outcomes.

## Methods

2

### Design

2.1

This is a prospective, observational, single-center trial. The patients with FGIDs will be continuously enrolled in the outpatient clinic by experienced physicians from the Department of Gastroenterology at Peking Union Medical College Hospital, who will strictly adhere to the guidelines. The diagnosis of FGIDs adheres to the diagnostic criteria outlined in Rome IV (1), encompassing primarily functional dyspepsia, irritable bowel syndrome, functional constipation, and other FGIDs. The diagnostic criteria for the aforementioned diseases are elaborated in the inclusion criteria. Baseline data including age, sex, marital status, employment status, body mass index (BMI), FGIDs subclasses, scores of symptoms and quality of life were recorded. The simultaneous evaluation of HADS and vibraimage technology will be conducted. The clinical screening efficacy of vibraimage technology will be assessed by comparing with HADS, which serves as the gold standard. The patients will be divided into two groups according to HADS, that is, FGIDs with or without psychological disorders. Both groups will be treated with identical conventional therapies. Post-treatment assessments of symptom questionnaire, HADS and vibraimage technology outcomes will be followed up, which may show the influence of psychological factors and provide a theoretical basis for the significance of identification and treatment of comorbid psychological disorders in FGIDs patients. The trial design is presented in Figure 1, while the subsequent sections provide a comprehensive and detailed description of our trial.

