#### Inclusion criteria

2.2.1

Age 18–80 years.The patients diagnosed with FGIDs during outpatient visits to the Department of Gastroenterology at Peking Union Medical College Hospital and who will provide consent for follow-up treatment and care. The study will primarily enroll patients who meet the Rome IV criteria (18) for functional dyspepsia, irritable bowel syndrome, functional constipation, and other FGIDs. Other FGIDs encompass chronic diarrhea, centrally mediated abdominal pain syndrome, functional esophageal disease, and functional anorectal disease.The patients must provide consent for the collection of facial video and completion of HADS psychological self-assessment.The patients must consent to undergo conventional treatment for FGIDs.The patients are able to sign the informed consent.

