#### Exclusion criteria

2.2.2

The patients who fulfill any of the following criteria will be excluded:

Age under 18 years old or over 80 years old.The patients presenting with celiac disease, inflammatory bowel disease, or other organic gastrointestinal disorders are typically diagnosed based on evident structural abnormalities or pathological changes. This comprehensive evaluation includes a detailed medical history, thorough physical examination, and auxiliary diagnostic tests.The patients presenting with secondary gastrointestinal motility disorders due to primary diseases such as cholecystitis, pancreatitis, hyperthyroidism, diabetes, chronic renal insufficiency, and neurological diseases.The patients who are reluctant to seek medical treatment and attend regular follow-up appointments at our hospital.The patients are either pregnant or lactating.The patients with severe comorbidities that impact medication management, such as severe hepatic insufficiency, renal failure, and congestive heart failure. The exclusion of such patients is a precautionary measure to avoid potential adverse drug reactions and to maintain the efficacy and safety of the study’s intervention.The current medication regimen includes antipsychotics, spasmolytics, antidiarrheals, probiotics, antibiotics, and other pharmacological agents utilized for the management of abdominal pain, intestinal peristalsis disorders, and gastrointestinal motility disturbances.

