### Conventional treatment

2.5

Patients enrolled in the study with FGIDs will receive conventional specialty care in gastroenterology. The clinician needs to determine which symptom features are dominant, and which treatment (s) are most likely to lead to improvement. Certain patients may find simple, cost-effective interventions such as laxatives or anti-diarrheal medicine (2). Treatment principles for patients with the same subtype of FGIDs are consistent, but actual treatment plans may vary slightly based on individual patient circumstances. The conventional treatment in this study does not encompass the utilization of psychotherapeutic drugs and psychotherapy.

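### The Likert ≥4 comparison between non-randomised HADS groups should be stratified by FGID subtype: subtype guides treatment, and the only stated test for proportions is a crude chi-square

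*Protocol article*

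**What the plan says.** All references are to the protocol article.

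- **Abstract and 2.1 Design.** The second aim is to "observe the therapeutic outcomes of FGIDs patients with or without comorbid psychological disorders after the same conventional treatment". Section 2.1 forms the groups by HADS and adds: "Both groups will be treated with identical conventional therapies".
- **2.5 Conventional treatment.** "The clinician needs to determine which symptom features are dominant, and which treatment (s) are most likely to lead to improvement". The examples given act in opposite directions: "Certain patients may find simple, cost-effective interventions such as laxatives or anti-diarrheal medicine". Consistency is claimed within a subtype: "Treatment principles for patients with the same subtype of FGIDs are consistent, but actual treatment plans may vary slightly based on individual patient circumstances". For all patients, "The conventional treatment in this study does not encompass the utilization of psychotherapeutic drugs and psychotherapy".
- **2.2.1 Inclusion criteria.** The cohort covers "functional dyspepsia, irritable bowel syndrome, functional constipation, and other FGIDs". The last category itself combines several different conditions, chronic diarrhea among them.
- **2.3 Baseline data collection.** FGID classification and treatment process are recorded. Prescribers do not know the HADS or vibraimage results.
- **2.6.2.** The primary prognosis endpoint is the proportion with Likert ≥4. The questionnaire is given after 4 weeks, and neither group gets anything beyond standard care.
- **2.7 Sample size calculation.** Improvement is 57% against half of that, and the target is 98 patients.
- **2.9 Descriptive statistics.** A chi-square test is given for the difference between the two groups. It is tied to no particular endpoint and no adjustment is mentioned. The logistic regression in the same section models whether a patient has a psychological disorder, not whether the patient improves.

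**The concern.** The follow-up comparison is meant to inform the influence of psychological factors on treatment outcome. HADS status is observed, not assigned, so the two groups may contain different proportions of each subtype. That matters in two ways. Because treatment follows subtype, a different subtype mix brings a different regimen mix. And subtype may affect four-week improvement by itself, even under one regimen.

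A crude difference in the proportion with Likert ≥4 contains both components, and an unadjusted chi-square cannot separate them from an effect of psychological status. At stake is the attribution of the difference. The variable that would largely settle the matter is already being collected.

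**Working it through.** **1. The plan's own figure.** Inputs from section 2.7: P1 = 0.57, P2 = 0.57/2 = 0.285, α = 0.05 (taken as two-sided), power 0.80, 1:1 allocation, 10% loss. With unpooled variance:

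n = (1.96 + 0.842)² × (0.57×0.43 + 0.285×0.715) / 0.285² = 43.4, so 44 per group (88 evaluable). Then 44/0.9 = 48.9, so 49 per group, or **98** in total. The stated figure is reproduced and is not disputed.

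**2. Size of the bias if psychological status has no effect.** The article gives no subtype shares and no response by subtype, so everything here is assumed. Take four subtypes with average improvement 57%. One better-responding subtype has a share d higher in the group without disorder, one worse-responding subtype has a share d lower there, and their improvement rates differ by g. The crude difference is then d × g.

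| Scenario | Mix, no disorder | Mix, disorder | Improvement by subtype | Crude difference |
|---|---|---|---|---|
| A (10 points) | .30, .25, .25, .20 | .20, .25, .25, .30 | .62, .57, .57, .52 | .575 − .565 = .01 |
| B (20 points) | .35, .25, .25, .15 | .15, .25, .25, .35 | .67, .57, .57, .47 | .590 − .550 = .04 |
| C (30 points) | .40, .25, .25, .10 | .10, .25, .25, .40 | .72, .57, .57, .42 | .615 − .525 = .09 |

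The planned effect is 57 − 28.5 = 28.5 points.

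**3. False-positive rate.** Simulation with 200,000 runs per cell, two-sided 0.05, uncorrected chi-square against Cochran-Mantel-Haenszel (CMH) without continuity correction:

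| Per group | Test | No imbalance | A | B | C |
|---|---|---|---|---|---|
| 44 | crude | 4.8% | 5.0% | 6.4% | 13.3% |
| 44 | CMH | 4.9% | 4.9% | 4.9% | 4.9% |
| 124 | crude | 4.7% | 5.1% | 9.5% | 29.0% |
| 124 | CMH | 4.9% | 5.1% | 4.9% | 5.0% |

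A repeat with 100,000 runs gave crude rates of 4.9%, 6.6% and 13.5% at 44 per group. Exact binomial enumeration around 57% gave 4.9%, 6.2% and 12.5%. The 124 rows (276 × 0.9 / 2) apply only if the whole diagnostic cohort is followed and splits evenly.

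**4. Size of the bias if the planned effect is real.** With improvement halved within every subtype, the crude differences are .575 − .2825 = 29.25 points (A), .590 − .275 = 31.5 points (B) and .615 − .2625 = 35.25 points (C). Against the subtype-balanced 28.5 points they overstate by 0.75, 3.0 and 6.75 points. Imbalance in the other direction would understate the effect.

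**5. Price of stratifying, 44 per group, improvement halved within subtype.** With equal mix, power is 78.0% crude and 76.7% CMH. CMH power is 76.2% under A, 74.1% under B and 69.6% under C. If 88 evaluable patients were spread evenly over four subtypes, each stratum would hold 88/4 = 22, or 11 per group.

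**The case against.** **The wording is about groups, not patients.** A reader might infer that sections 2.1 and 2.5 contradict each other and that the comparison is therefore invalid, or that treatment could follow HADS status. The article does not support that. The sentence in 2.1 starts from the two groups and can fairly be read as saying that care does not depend on HADS group. Prescriber masking (2.3), the absence of extra interventions (2.6.2), the exclusion of psychotherapeutic drugs and psychotherapy from care (2.5) and the exclusion of patients already on relevant drugs (2.2.2) all support that reading. Section 2.5 is open about variation and calls it slight. So the wording issue is editorial and changes no result, and the abstract's phrase is accurate as it stands. These safeguards do not, however, stop subtype mix from differing between the groups.

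**An adjusted analysis may exist elsewhere.** This is a condensed article, and an unseen full protocol or SAP may already contain one. That is why the point is a recommendation about the analysis the article states, not a claim that adjustment is missing.

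**No harm is demonstrated.** Every bias input is assumed. At the planned size the crude test is close to nominal in the first two scenarios, and only the extreme one reaches 13%. Section 2.1 also hedges its inference. All of this stands and limits the severity.

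**Stratifying is not free or complete.** Subtype is itself a symptom-based diagnosis that psychological state might influence, so stratification may remove part of a total effect. It leaves regimen variation within a subtype, particularly within the mixed *other* category. The one-point power loss holds only with equal mix. These limits also stand and belong beside the result.

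**Conclusion.** The concern holds as a minor point of analysis. The Likert ≥4 comparison is between non-randomised groups that mix subtypes treated differently, and the only two-group test stated for proportions makes no allowance for this. A difference in subtype mix could be taken for an effect of psychological status.

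The size of any bias is unknown. Under the assumed inputs it is 1, 4 or 9 points against a planned 28.5, with null rejection of about 5%, 6.5% and 13% at 44 per group. It becomes material only when subtype imbalance and response gap are both large. The larger figures at 124 per group should not be cited as the expected case, because they assume follow-up of the whole cohort.

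A stratified comparison estimates the psychological effect within subtype. Subtype therefore removes the between-subtype part of the regimen difference, but not all of it.

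**What to change.** - Make the Likert ≥4 comparison stratified by the recorded FGID subtype the governing analysis, by Cochran-Mantel-Haenszel or by logistic regression with subtype as a covariate. Show the crude chi-square as descriptive, so that it is clear in advance which result counts if they differ.
- Do not stratify on or adjust for treatment received: it follows dominant symptoms, which psychological state may influence. Tabulate it by HADS group for description only.
- State that the estimate is within subtype and that regimen variation inside a subtype remains.
- Editorial: in section 2.1, replace *identical conventional therapies* with *the same subtype-specific conventional care, chosen without knowledge of HADS*. The abstract may stay as it is.

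**Cost.** No new data or patients are needed: one change of governing analysis, one descriptive table and one phrase. The price is small strata (about 11 per group per subtype if evenly spread) and the power loss shown in the working: about 1 point with equal mix, with power falling to about 70% in the most imbalanced scenario.
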